## Abstract

**Background:**

Lung dysfunction commonly occurs after cardiopulmonary bypass (CPB). Randomized evidence suggests that the presence of expiratory flow limitation (EFL) in major abdominal surgery is associated with postoperative pulmonary complications. Appropriate lung recruitment and a correctly set positive end-expiratory pressure (PEEP) level may prevent EFL. According to the available data in the literature, an adequate ventilation strategy during cardiac surgery is not provided. The aim of this study is to assess whether a mechanical ventilation strategy based on optimal lung recruitment with a best PEEP before and after CPB and with a continuous positive airway pressure (CPAP) during CPB would reduce the incidence of respiratory complications after cardiac surgery.

**Methods/design:**

This will be a single-center, single-blind, parallel-group, randomized controlled trial. Using a 2-by-2 factorial design, high-risk adult patients undergoing elective cardiac surgery will be randomly assigned to receive either a best PEEP (calculated with a PEEP test) or zero PEEP before and after CPB and CPAP (equal to the best PEEP) or no ventilation (patient disconnected from the circuit) during CPB.

The primary endpoint will be a composite endpoint of the incidence of EFL after the weaning from CPB and postoperative pulmonary complications.

**Discussion:**

This study will help to establish a correct ventilatory strategy before, after, and during CPB. The main purpose is to establish if a ventilation based on a simple and feasible respiratory test may preserve lung function in cardiac surgery.

**Trial registration:**

ClinicalTrials.gov, ID: NCT02633423. Registered on 6 December 2017.

**Electronic supplementary material:**

The online version of this article (10.1186/s13063-018-3046-0) contains supplementary material, which is available to authorized users.

## Background

General anesthesia is associated to a decreased functional residual capacity (FRC) [1]. Many pathophysiological factors, such as high oxygen concentrations delivered at anesthesia induction, supine positioning, muscle relaxation, large amounts of intravenously administered fluids, and also the inflammatory reaction, may be implicated. Due to this phenomenon, the closing capacity may exceed the FRC during general anesthesia, leading to the collapse of the small airways, clinically detectable as expiratory flow limitation (EFL), and atelectasis. Several factors contribute to EFL during general anesthesia, including the clinical characteristics of the patients, anesthesia induction by itself, and also cardiopulmonary bypass (CPB). The presence of tidal EFL implies increased ventilation/perfusion ratio mismatch, increased airways’ resistance, risk of peripheral airways’ injuries, and, histologically, rupture of the alveolar attachments to the respiratory bronchioles, damage of the bronchiolar epithelium and increased number of polymorphonuclear leukocytes in the alveolar walls. The presence of EFL can be easily detected during general anesthesia by using the positive expiratory pressure (PEEP) test. Expiratory flow limitation was detected in a supine position in 10% of the patients during the pre-surgery evaluation. However, this percentage increased to 52% at the end of surgery. In other words, 42% of the patients treated with zero PEEP became flow limited during surgery [1]. EFL is important not only because older patients can be flow limited before surgery, but, more interestingly, because they can develop EFL during surgery.

There are numerous clinical situations associated with the presence of EFL [2, 3], such as heart failure, chronic obstructive pulmonary disease, obesity, sleep apnea, and bronchiectasis. Cardiopulmonary bypass is associated with direct lung damage. Pulmonary atelectasis, apnea, ischemia during CPB and activation of proteolytic enzymes in the pulmonary circulation influence the incidence of postoperative pulmonary dysfunction after cardiac surgery [4–7]. Moreover, although postoperative impairment could be transient and respiratory function can recover shortly after surgery, some patients may develop respiratory complications both in the intraoperative or postoperative period. The incidence of postoperative pulmonary complications (PCCs) ranged from 3 to 16% following coronary artery bypass grafting and 5–7% following cardiac valvular surgery.

The consequence of a low-tidal-volume ventilation strategy can be avoided by the application of PEEP. The use of PEEP prevents the decrease of FRC and can stabilize the small airways and improve respiratory mechanics and oxygenation, provided that PEEP is high enough to prevent the development of EFL. There are several studies that compare high versus low PEEP levels during general anesthesia for major abdominal surgery [1, 8–11], far fewer in adult cardiac surgery. Since the presence of EFL has been previously associated with PPCs after major abdominal surgery [2] and cardiac surgery [12], we hypothesized that the use of PEEP able to avoid EFL should reduce the PPCs during cardiac surgery.

### Objectives

EFL occurs when, at a given lung volume, the expiratory flow is independent of the patient’s expiratory effort or on an increase of elastic recoil pressure [13]. The purpose of this study is to investigate whether an optimal lung recruitment strategy before CPB, based on a best PEEP calculated according to the PEEP test, and during CPB, with a continuous positive airway pressure (CPAP) instead of no ventilation, would reduce the incidence of the EFL phenomenon and of PPCs after cardiac surgery, compared with no PEEP before, during, and after CPB.

The main hypothesis of this trial is that an adequate lung recruitment based on the best PEEP before and after CPB, defined as the minimum PEEP level necessary to avoid the EFL phenomenon, and/or an adequate level of CPAP during could reduce lung injury following cardiac surgery.

## Methods/design

### Trial design

This will be a single-center, single-blind, parallel-group, randomized controlled trial. Using a 2-by-2 factorial design, high-risk adult patients undergoing elective cardiac surgery will be randomly assigned to receive either a best PEEP (calculated with a PEEP test) ventilation or a zero PEEP strategy before and after CPB and CPAP (equal to the best PEEP) or no ventilation (patient disconnected from the circuit) during CPB.

We will recruit all patients that will match the eligibility criteria at the preoperative evaluation. The protocol structure was written in according to the Consolidated Standards of Reporting Trials (CONSORT) 2010 Statement [14] and follows the Standard Protocol Items: Recommendations for Interventional Trials (SPIRIT) Statement [15]. The SPIRIT Figure of this trial is illustrated in Fig. 1. The SPIRIT Checklist of this trial can be found in Additional file 1. Patients will also be evaluated in terms of (1) shunt fraction and (2) data of respiratory mechanics, such as static compliance, flow, and additional resistance. All these parameters will be determined: (1) immediately after anesthesia induction, (2) before CPB, (3) during CPB, (4) off pump, and (5) end of surgery.

**Fig. 1 Fig1:**
[figure not shown]
The Standard Protocol Items: Recommendations for Interventional Trials (SPIRIT) Figure of this trial

The study has been registered at ClinicalTrials.gov with the registration number NCT02633423 on 6 December 2017.

### Participants

In order to obtain Ethics Committee approval, documentation was submitted in December 2017 and we are currently waiting for approval. We intend to enroll patients aged 18 years or over who are undergoing elective cardiac surgery with planned use of CPB, aortic cross-clamping, median sternotomy, and two-lung ventilation. All patients will provide written informed consent before their inclusion in the trial. The inclusion and exclusion criteria are shown in Table 1.

**Table 1 Tab1:** Inclusion/exclusion criteria

Eligibility criteria	
Inclusion criteria: • Elective cardiac surgery, with median sternotomy and two-lung ventilation • Patients scheduled for mitral valve regurgitation and/or aortic valve regurgitation surgery, performed with CPB and aortic cross-clamping • Adult patients (age 18 years or older) • Ability to provide informed consent • High risk for respiratory dysfunction, defined as 1 of: preoperative hypoxemia (arterial oxygen saturation < 92% in room air or arterial oxygen partial pressure < 60 mmHg at blood-gas analysis or a PaO_2_/FiO_2_ ratio < 200 at basal blood-gas analysis); preoperative obesity (BMI > 30); preoperative ejection fraction < 50%; preoperative NYHA class > II Age > 65 years [25].	Exclusion criteria: • Non-elective cardiac surgery • Anticipated circulatory arrest, TAVI, Mitraclip • Patient’s refusal • Pregnancy • Thoracotomic approach, with one-lung ventilation • Previous pulmonary resection • Patients with acute kidney injury requiring dialysis • Patients with chronic kidney insufficiency (stage III or greater) • Patients already intubated before arrival in operating theater • Pneumonia in the previous 30 days

*BMI* body mass index, *CPB* cardiopulmonary bypass, *NYHA* New York Heart Association, *TAVI* transcatheter aortic valve implantation

### Endpoints

The primary endpoint will be a composite endpoint of the incidence of EFL after CPB and of PPCs at 5 days after surgery (see Table 2 for complete definition of PPCs). Before/after sternotomy, a PEEP test will provide the best PEEP value, that will be the least value of PEEP for which closing capacity does not exceed the FRC, leading to the avoidance of EFL and atelectasis. In practice, the EFL phenomenon will be assessed at different PEEP levels, until the abrupt decrease in end-expiratory pressure will cause an increment in expiratory flow. At this level the patient will not be flow-limited and this will be considerate his best PEEP for the rest of surgery.

**Table 2 Tab2:** Definition of postoperative pulmonary complications (PPCs), Jammer et al*.* [24]

Complication	Definition
Respiratory infection	Patient has received antibiotics for a suspected respiratory infection and met one or more of the following criteria: new or changed sputum, new or changed lung opacities, fever, white blood cell count > 12 × 10^9^ l^-1^
Respiratory failure	Postoperative PaO_2_ < 8 kPa (60 mmHg) on room air, a PaO_2_:FIO_2_ ratio < 40 kPa (300 mmHg) or arterial oxyhemoglobin saturation measured with pulse oximetry < 90% and requiring oxygen therapy
Pleural effusion	Chest radiograph demonstrating blunting of the costophrenic angle, loss of sharp silhouette of the ipsilateral hemidiaphragm in upright position, evidence of displacement of adjacent anatomical structures or (in supine position) a hazy opacity in one hemithorax with preserved vascular shadows
Atelectasis	Lung opacification with a shift of the mediastinum, hilum, or hemidiaphragm toward the affected area, and compensatory over-inflation in the adjacent non-atelectatic lung
Pneumothorax	Air in the pleural space with no vascular bed surrounding the visceral pleura
Bronchospasm	Newly detected expiratory wheezing treated with bronchodilators
Aspiration pneumonitis	Acute lung injury after the inhalation of regurgitated gastric contents

*PaO*_*2*_ arterial partial oxygen pressure, *FiO*_*2*_ fraction of inspired oxygen

The secondary endpoints will be the evaluation of the following:Readmission to the intensive care unit (ICU)Need for re-intubationNeed for non-invasive ventilationDuration of mechanical ventilationPostoperative infectionsMajor adverse cardiac events (MACE; see Table 3 for complete definition of MACE)Length of the ICU and hospital stay30-day and 1-year mortality

**Table 3 Tab3:** Definition of major adverse cardiac events (MACE), Jammer et al. [24]

Complication	Definition
Non-fatal cardiac arrest	An absence of cardiac rhythm or presence of chaotic rhythm requiring any component of basic or advanced cardiac life support
Acute myocardial infarction	Increase and gradual decrease in troponin level or a faster increase and decrease of creatine kinase isoenzyme as markers of myocardial necrosis in the company of at least one of the following: ischemic symptoms, abnormal Q waves on the ECG, ST-segment elevation or depression; coronary artery intervention (e.g., coronary angioplasty) or a typical decrease in an elevated troponin level detected at its peak after surgery in a patient without a documented alternative explanation for the troponin elevation
Congestive heart failure	New in-hospital signs or symptoms of dyspnea or fatigue, orthopnea, paroxysmal nocturnal dyspnea, increased jugular venous pressure, pulmonary râles on physical examination, cardiomegaly, or pulmonary vascular engorgement
New cardiac arrhythmia	ECG evidence of atrial flutter, atrial fibrillation, or second- or third-degree atrioventricular conduction block
Angina	Dull, diffuse, substernal chest discomfort precipitated by exertion or emotion and relieved by rest or glyceryl trinitrate

*ECG* electrocardiogram

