### EFL determination

The determination of EFL during general anesthesia and neuromuscular blockade will be performed using the PEEP test. This test is based on a sudden decrease of expiratory resistance obtained by a subtraction of 3 cmH_2_O of PEEP during expiration (Fig. 3). A patient will be considered to have EFL if reducing PEEP by 3 cmH_2_O will not increase expiratory flow when compared with the previous breath (panel B). If expiratory flow will increase with PEEP reduction, the patient will be considered not flow limited (panel A). All loops will be saved in electronic format for further analysis.

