### Statistical considerations

#### Sample size

Sample size calculation was based on a two-sided α error of 0.05 and a 80% power (β). On the basis of our experience, we anticipate that the 50% of patients with ventilation cessation during CPB and no PEEP before and after CPB will reach the composite endpoint of EFL after CPB and respiratory complications at 5 days, while only the 30% of the patients treated with an optimal ventilatory strategy will develop this composite endpoint. Including a drop-out fraction of 10%, we will enroll 51 patients per group, 204 in total.

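### For the PEEP factor, the EFL half of the primary composite depends on a ventilator setting the plan does not fix, and no listed endpoint reports PPCs alone

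*Protocol article*

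**What the plan says.** - **Primary endpoint** (Endpoints): "The primary endpoint will be a composite endpoint of the incidence of EFL after CPB and of PPCs at 5 days after surgery". The abstract places the EFL component after weaning from bypass.
- **Test** (EFL determination): "A patient will be considered to have EFL if reducing PEEP by 3" cmH2O leaves expiratory flow no higher than on the breath before.
- **Treated arm** (Endpoints): PEEP is titrated around sternotomy until the test is negative. "At this level the patient will not be flow-limited and this will be considerate his best PEEP for the rest of surgery". The Interventions section places this titration straight after induction. Both are before bypass.
- **Control arm** (Trial design; Interventions): zero PEEP before and after bypass.
- **Time-points** (EFL determination): EFL is read after the recruitment maneuver, before sternosynthesis and before leaving the operating room, as well as earlier. None of these is named as the endpoint reading, and no PEEP for it is given.
- **Aims**: the abstract asks whether the strategy "would reduce the incidence of respiratory complications after cardiac surgery". The Objectives section names both EFL and PPCs.
- **Background rates**: EFL 52% at the end of surgery; PPCs 3–16% after bypass grafting and "5–7% following cardiac valvular surgery".
- **Secondary endpoints** (Endpoints): neither EFL alone nor PPCs alone is listed.

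**The concern.** The PEEP factor sets the condition under which half of its own primary endpoint is measured. One arm carries a PEEP selected because the EFL test is negative there. The other is at zero, where the printed test needs an extra step that is not described. Unless the reading conditions are fixed, the same lungs could be scored differently by arm because of the setting at that moment. The Interventions section says the trial focuses on data that physician management cannot influence, which does not fit an EFL reading that may follow the allocated PEEP.

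This matters because EFL is probably the commoner component. A significant composite could then reflect EFL alone, and a reader who takes the abstract's aim at face value would conclude that respiratory complications fell. No listed endpoint would show directly whether they did.

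**Working it through.** **Inputs from the article.** Composite 50% v 30%, two-sided alpha 0.05, 80% power, 10% drop-out, 204 patients (Sample size). EFL 52% and the PPC rates above (Background).

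**Assumptions.** EFL and PPCs are independent. PPCs are equal in both arms. A fraction k of EFL-positive lungs reads negative only because of the PEEP in use. Evaluable patients per factor level: 102 × 0.9 ≈ 92.

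**1. The plan's own figure.** Per factor level, n = [1.96√(2 × 0.4 × 0.6) + 0.842√(0.5 × 0.5 + 0.3 × 0.7)]² / 0.2² = 93. Then 2 × 93 × 1.1 = 204.6, or 51 per cell and 204 in total. The size therefore reproduces as a comparison of factor margins. Power with 92 per level is 79.6%.

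**2. How much of the composite is EFL.** Every patient with a PPC is an event, so the EFL-only share at a 50% composite is 1 − PPC/0.50. With equal PPCs, the EFL rates needed to produce 50% v 30% are 1 − 0.50/(1 − PPC) and 1 − 0.70/(1 − PPC).

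| PPC rate | EFL-only share | EFL needed, control v treated |
|---|---|---|
| 5% | 90% | 47.4% v 26.3% |
| 7% | 86% | 46.2% v 24.7% |
| 16% | 68% | 40.5% v 16.7% |
| 30% | 40% | 28.6% v 0% |

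EFL can carry the whole planned effect. The last row is the limit: with no PPC effect, PPCs cannot exceed the planned treated rate of 30%.

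**3. Same lungs, same PPCs, different setting.** Composite = 1 − (1 − EFL)(1 − PPC), with EFL 0.52 in control and 0.52(1 − k) under best PEEP, and PPC 6% (middle of 5–7%). Control: 1 − 0.48 × 0.94 = 54.9%.

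| k | Composite, best PEEP | Chance of p<0.05 |
|---|---|---|
| 25% | 42.7% | 38% |
| 40% | 35.3% | 76% |
| 50% | 30.4% | 92% |

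With PPCs at 30% and k = 50%, the composite is 66.4% v 48.2% and the chance is 71%.

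**4. The reverse case.** Suppose treatment abolished every PPC and left EFL unchanged at 30–52%. The composite would reach p<0.05 with probability 7–11% (PPC 7%) or 18–35% (PPC 16%). At the background rates, the composite responds to EFL and hardly to PPCs.

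**5. PPCs alone.** For a 40% relative reduction (an assumption; the article gives no PPC effect) with 92 per level, exact power is 9% (5% to 3%), 12% (7% to 4.2%) and 25% (16% to 9.6%).

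**The case against.** Several stronger readings are tempting, and the article does not support them.

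- **That EFL is stated to be read at each arm's own PEEP.** It is not stated. It is the plain inference from a test that compares with the previous breath while the allocated PEEP is in use. The Endpoints section also describes assessment at several PEEP levels, so changing PEEP for the test is envisaged. If the control setting is raised to permit the test, the level is still unstated and could still differ between arms.
- **That the treated arm is EFL-negative by definition at the endpoint.** This holds only at titration, before bypass. The Background names bypass as a cause of EFL, and a recruitment maneuver intervenes. Whether the chosen PEEP still prevents EFL afterwards is a real question.
- **That an EFL difference would be worthless.** The Background treats EFL as injurious, and reducing it is a stated purpose in Objectives. Part of any difference may be the intended effect. The masked fractions have no source in the article.
- **That EFL supplies nearly all events.** The 52% cites a source the Background lists among studies of major abdominal surgery. The quoted PPC rates come without a definition, whereas Table 2 counts any radiographic pleural effusion and a PaO2/FiO2 ratio below 300 mmHg, and Table 1 selects patients at respiratory risk. PPCs may well exceed 7%.
- **That both factors are affected.** Each CPAP level contains the same mix of PEEP arms, so this artefact does not touch the CPAP contrast.

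It is also fair that PPCs are collected on every patient, that re-intubation, non-invasive ventilation and infections give partial information, and that operating detail may sit in a full protocol. What remains is that the printed definition does not work unaided at zero PEEP, the endpoint reading is not identified, and the printed secondary list omits both components.

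**Conclusion.** The point stands for the PEEP factor. The EFL component depends on the reading conditions, and the article fixes neither the PEEP nor the single post-bypass time-point. EFL probably supplies most composite events at the quoted background rates: 68–90% EFL only with PPCs of 5–16%, falling to about 40% if PPCs reach 30%. The composite can therefore favour PEEP with PPCs unchanged. The chance of p<0.05 is 38–92% if the setting masks 25–50% of EFL, given 52% EFL, 6% PPCs, independence and 92 evaluable per level. These figures show what is possible under assumed masking; they do not predict it. A reader might infer that a positive result would be a tautology or that PEEP has no benefit, but the article supports neither. The supported conclusion is narrower: a composite result for PEEP cannot by itself show that respiratory complications fell.

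**What to change.** 1. **List the components.** In Endpoints, add EFL after CPB alone and PPCs at 5 days alone as named secondary endpoints, each with a relative risk and 95% confidence interval for each factor. State that a reduction in respiratory complications will be claimed only from the PPC result, and acknowledge its low power (about 9–25% in the cases above). The data are already collected. The cost is a narrower claim if only EFL moves.

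2. **Reconcile the EFL reading.** Bring Endpoints, Interventions and EFL determination (with its time-point list) into agreement on how the PEEP test is done in the zero-PEEP arm and which post-bypass reading is the endpoint. This is wording, settled with the clinical team; recruitment had not begun when the article was written.

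3. **Add a common-condition reading if feasible.** Where the clinical team finds it acceptable, also record EFL under the same test conditions in all four cells and use it as a sensitivity analysis. The cost is a few extra breaths of testing. Replacing the endpoint reading with this one would change what is estimated and could undo the 50% v 30% planning assumption, so it is not proposed as a replacement. No PEEP level is proposed here.

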### Interventions (randomization and treatment protocol)

Once the patient has provided informed consent, the investigator (e.g., the anesthesiologist in the operating theater) logs into a dedicated on-line portal (www.eflvent.it) to obtain the allocation arms. The randomization will be in a 1:1 ratio between the parallel groups, in blocks of 20 patients. From that moment, the online data will be anonymous and, in any event, the patient will be analyzed according to the “intention-to-treat” principle.

To reduce the bias, data will be collected by trained observers, trained accordingly to Good Clinical Practice (GCP) guidelines [16, 17], who will not participate to patient care. Furthermore, we decided to focus on clinically relevant data that cannot be influenced by physician management. Caregivers will be interviewed daily about the occurrence of postoperative adverse events. The patients will be blinded to the allocation arm.

All patients will receive lung protective ventilation, with a tidal volume of 7 ml/Kg of ideal body weight (IBW), a respiratory frequency titrated to maintain normocapnia, assessed by seriated blood-gas analyses. FiO_2_ will never be higher than 80%, except for the blood samples obtained for shunt fraction calculation.

Patients will be randomized, immediately before surgery, to receive either a PEEP equal to the best PEEP, assessed with a PEEP test, immediately after the induction of anesthesia or to zero. All patient will be furthermore randomized to receive either a CPAP equal to the best PEEP or a zero PEEP strategy (with disconnection from anesthesia circuit) during CPB. The two randomizations will be independent each from other.

During CPB our goal will be to maintain PaO_2_ between 200 and 250 mmHg in order to avoid hyperoxia-induced lung injury; moreover, the hematocrit will be maintained above 24% [18].

During weaning from CPB we will perform a single alveolar recruitment maneuver (RM). This RM will be performed manually by the anesthesiologist with a gas mixture of oxygen and air (with an inspired oxygen fraction lower than 80%) at the end of procedure. After CPB, this RM will be performed manually, in correspondence to the surgical de-airing procedure. Airway pressure will be kept at 40 cmH_2_O for at least 10 s. The flowchart in figure 2 (Fig. 2) resume the enrollment and allocation process.

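### The protocol does not require the post-induction PEEP test to be recorded before the allocation is released, so baseline EFL and the best-PEEP value can be read with the arm known

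*Protocol article*

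**What the plan says.** **Who opens the allocation, and when.** The Interventions section reads: "Once the patient has provided informed consent, the investigator (e.g., the anesthesiologist in the operating theater) logs into a dedicated on-line portal", and the purpose of the log-in is "to obtain the allocation arms". It then adds: "Patients will be randomized, immediately before surgery".

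**When the best PEEP is found.** The same section describes the best PEEP as "assessed with a PEEP test, immediately after the induction of anesthesia or to zero". For the second factor it says: "All patient will be furthermore randomized to receive either a CPAP equal to the best PEEP or a zero PEEP strategy". No separate time is given for opening the CPAP allocation. The Endpoints section times the test differently: "Before/after sternotomy, a PEEP test will provide the best PEEP value".

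**Baseline reading.** The EFL determination section lists six time-points for EFL, the first after induction. Neither that list nor Table 4 restricts the measurements by arm.

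**Masking.** The design is single-blind, and only patients are said to be blinded. Data collectors are outside patient care but are not said to be unaware of the arm. All loops are stored electronically for later analysis, with no mention of a masked reading.

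**The concern.** The PEEP test is read by judgement. The operator decides whether expiratory flow rose when PEEP was cut by 3 cmH2O. The caption of Fig. 3 accepts that a flow-limited patient may still show a short early rise, so the line between the two classes needs interpretation. That reading gives the baseline EFL status, and the same method gives the best-PEEP value.

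If the anesthesiologist already knows the arm, both become allocation-aware measurements taken after randomization. Two things are at stake:

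- Baseline EFL separates limitation that was already present from limitation that develops during surgery. EFL after CPB is part of the primary composite, so a reader of the results will look at the baseline figure. It should differ between arms only by chance.
- The best-PEEP value sets the level delivered in three of the four groups: both best-PEEP groups, and zero PEEP with CPAP, because CPAP equals the best PEEP. It should come from the patient and the test, not from knowledge of the group.

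A lesser matter is the interval between allocation and treatment. A patient who is allocated and then not treated stays in the intention-to-treat set and dilutes the contrast.

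**Working it through.** **Step 1: order of events.** The statements side by side:

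| Event | Timing given | Section |
|---|---|---|
| Consent | Before log-in | Interventions |
| Log-in to obtain the arms | After consent, for example by the theatre anesthesiologist | Interventions |
| Randomization of PEEP | Immediately before surgery | Interventions |
| Test that sets best PEEP | Immediately after induction | Interventions |
| Test that sets best PEEP | Before/after sternotomy | Endpoints |
| First EFL reading | After induction | EFL determination |

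The natural order is consent, allocation, induction, test. It is not the only possible one. Consent is a precondition for log-in rather than the stated moment of allocation, and a randomization immediately before surgery could fall after induction. That both factors are opened together rests only on the plural used for the arms. No text requires the test to be recorded before the arm is known.

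**Step 2: timing of the dose-setting test.** The six rows of Table 4 match the six listed EFL time-points in order, so its before-sternotomy row corresponds to the post-induction reading. The word before in the Endpoints section therefore agrees with the Interventions section. Only the word after conflicts with it.

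**Step 3: patients touched.** There are 51 per group in four groups, 4 × 51 = 204, all with a baseline EFL reading. The delivered level depends on the best-PEEP value in 3 × 51 = 153.

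**Step 4: the planned sample size.** Inputs from the Sample size section: 50% versus 30%, two-sided 0.05, 80% power, 10% drop-out. With the unpooled normal approximation:

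- n per level = (1.96 + 0.8416)² × (0.50 × 0.50 + 0.30 × 0.70) / 0.20² = 7.849 × 0.46 / 0.04 = 90.3, so 91
- 91 / 0.90 = 101.1, so 102 per level of each factor
- 2 × 102 = 204, or 51 per group, which is the plan's figure

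**Step 5: dilution, under assumed rates.** Suppose a share d of the treated level is allocated, stays in the analysis, is never treated and keeps the 50% event rate. The treated rate becomes p2 = 0.30 + 0.20d. With n = 102 per level, p1 = 0.50 and p̄ the mean of p1 and p2:

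power = Φ{[(p1 − p2) − 1.96 √(2p̄(1 − p̄)/n)] / √[(p1(1 − p1) + p2(1 − p2))/n]}

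| d (assumed) | p2 | Power |
|---|---|---|
| 0 | 0.30 | 83.5% |
| 5% | 0.31 | 79.4% |
| 10% | 0.32 | 74.7% |
| 15% | 0.33 | 69.6% |

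The protocol gives no value for d. The table shows what each level would cost, not what will happen.

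**The case against.** The strongest reply is that the order is inferred. Allocation immediately before surgery, by an anesthesiologist in theatre, could come after induction, and Fig. 2 may show the sequence. This stands, and it lowers confidence. It does not remove the point, because the text should fix the order either way.

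A second reply is that safeguards exist: observers outside patient care, and stored loops that can be audited. This stands in part. A masked re-reading would be possible, but none is stated, and it could not undo a level already set at the bedside.

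A third is that the Data analysis section describes no adjustment for baseline EFL and no subgroup by it, and that post-CPB EFL would still be read after allocation. Both are correct. They limit the benefit.

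Three stronger readings are tempting, and the documents do not support them:

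- A reader might infer that the CPAP effect is confounded because only the zero-PEEP, no-CPAP group has no use for a titrated value. No text says that group goes untested. The Endpoints section, the EFL determination section and Table 4 set no restriction by arm, and a recruitment maneuver follows at weaning, also without restriction.
- A reader might infer that the operator will choose between a post-induction and a post-sternotomy reading. The loose timing is a wording fault, and no text describes such conduct.
- A reader might infer that part of the drop-out allowance, 10% of 204 or about 20 patients, arises between allocation and anesthesia. Nothing says when drop-out occurs. The endpoint runs to day 5, so it can arise later.

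**Conclusion.** The point holds in a limited form and with moderate confidence. As naturally read, the Interventions section allows the baseline EFL reading and the best-PEEP determination to be made by someone who knows the arm, and nothing in the text prevents this. The article also gives two times for the best-PEEP determination that agree only in part.

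The size of any bias in the readings cannot be derived from the documents. The possible exposure is the baseline reading in all 204 patients and the delivered level in 153 of them. The interval between allocation and treatment is a secondary matter. If allocation is immediately before surgery the interval is short, at least for the PEEP factor, and its effect under intention to treat is mainly dilution. The power figures rest on assumed rates of non-treatment.

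The conclusion assumes that allocation precedes induction. If Fig. 2 or the full protocol places it after the test, only the need to say so in the text and the timing conflict remain. The sample size reproduces and is unaffected.

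**What to change.** In the Interventions section, state the order explicitly: the post-induction PEEP test, already scheduled for every patient, is done in the same way in all groups, and its result and loop are entered in the portal before the portal releases the allocation. Make that entry a required field for release.

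Reconcile the Interventions and Endpoints sections to one named time for the best-PEEP determination. Which time is for the investigators to decide. If they name one later than the post-induction test, the release rule above protects the baseline EFL reading, but protects the best-PEEP value only if release also waits for that later test.

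The benefit is a baseline reading and a best-PEEP value free of allocation knowledge, and a shorter interval in which an allocated patient can go untreated. The change does not mask the post-CPB EFL endpoint, which is a separate matter.

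The cost is protocol wording, one required portal field, and a little extra test time in the zero-PEEP, no-CPAP group if it would not otherwise be titrated. The Current trial status section says recruitment had not begun, so the change can be made before any patient is allocated. Total enrolment stays at 204.
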